## Statistics

### Sample size calculation

The sample size for the present study has been estimated based on data of the EMSA-SG natural history study (Wenning et al. 2013). In this historical cohort, individuals with MSA showed an average EQ-5D score at baseline of 0.35 (95% CI 0.27–0.42), which worsened to 0.17 (95% CI 0.06–0.28) over an observational period of 18 months under standard care (Wenning et al. 2013). In other chronic medical conditions, treatment is considered to be positively associated with QoL, if the EQ-5D score change in the interventional group averages 0.08 points above that of the control group at follow-up (Kwakkenbos et al. 2013). If effective, we therefore estimate the MeDeMSA Care program to limit the baseline to 18 months EQ-5D worsening to 0.25 (± 0.25 standard deviation, SD) in the MSA individuals receiving personalized best medical care with integrated mobile palliative and telemedicine support, as needed. With an assumed significance level of 5% and a power of 80%, 46 individuals with MSA should therefore enroll in the trial to observe an effect of the personalized multidisciplinary care program compared to the standard care offered to the historical MSA cohort, including an expected drop-out rate of 10% over the study course.

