Building on the multidisciplinary expertise in MSA care at the Medical University of Innsbruck and its national and international partners, the Medical Decision Making in Multiple System Atrophy (MeDeMSA) Care study has been launched. It aims to evaluate whether a personalized, multidisciplinary care model, integrating mobile palliative care and telemedicine support, can attenuate QoL decline in prospectively recruited individuals with MSA by alleviating the symptomatic burden, ensuring continuity of care, and prioritizing individual healthcare preferences. QoL changes over 18 months are captured with the European QoL Questionnaire – 5 Dimensions – 5 Levels [EQ-5D-5L, (Rabin and de Charro 2001; Feng et al. 2021)] and compared to a matched historical European MSA cohort that received standard care [European MSA Study GroupEMSA-SG, cohort (Wenning et al. 2013)].

Secondary objectives of the MeDeMSA Care study are to assess the acceptance, safety, and cost effectiveness of such an integrated healthcare model, and are detailed in Table 1, along with their respective outcome measures. We here aim at sharing the MeDeMSA Care study design and operational protocols.

**Table 1 Tab1:** Primary and secondary objectives of the MeDeMSA Care Study (left) and respective outcome measures (right)

	Objective	Outcome measure
Quality of life	*Primary*	
	Impact of a multidisciplinary, personalized treatment plan including mobile palliative care (as needed) on the baseline to 18-months change in QoL of prospectively recruited MSA individuals, compared to sex-, age- (± 5 years), and disease duration- (± 12 months) matched MSA individuals from the historical EMSA-SG cohort^a^	- Baseline to 18-months EQ-5D-5L score change
	*Secondary*	
	Impact of a multidisciplinary, personalized treatment plan including mobile palliative care (as needed) on the baseline to 6- and 12-months change in QoL of prospectively recruited MSA individuals, compared to sex-, age- (± 5 years), and disease duration-(± 12 months) matched MSA individuals from the historical EMSA-SG cohort^a^	- Baseline to 6- and 12-months EQ-5D-5L score change - Baseline to 6-, 12- and 18-months changes in the MSA-QoL total score and subscores

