### Analysis sets and subgroups

For the primary objective (see Table 1), we will compare the prospectively recruited MeDeMSA Care cohort with data from the historical EMSA-SG cohort (Wenning et al. 2013), matched by age (± 5 years), sex, and disease duration (± 12 months). Disease duration is defined as the time from the onset of motor symptoms or selected autonomic features, including orthostatic hypotension, urinary urge incontinence, or incomplete bladder emptying. If exact matching is not possible due to unavailable controls, an alternative matching approach by categorizing individuals into subgroups based on age (< 60 versus ≥ 60 years) and disease duration (< 3 vs. ≥ 3 years) will be applied. To better characterize the MeDeMSA Care cohort and, secondarily, enable detailed comparisons between personalized best medical care with and without telemedicine, the EQ-5D-5L tool has been chosen for the present study (Janssen et al. 2013; Feng et al. 2021). This offers five response levels: no/slight/moderate/severe/extreme problems. For comparisons with the historical cohort, which used the EQ-5D-3L with three response levels (no/moderate/extreme problems), EQ-5D-5L responses will be grouped post-hoc and consistently applied across assessments (van Hout et al. 2012).

For secondary objectives (see Table 2), the MeDeMSA Care cohort will be divided into early versus advanced MSA (i.e., wheelchair-bound at the time of recruitment), and further sub-grouped by sex (male versus female), MSA phenotype [parkinsonian versus cerebellar (Wenning et al. 2022)], age (< 60 versus ≥ 60 years), and disease duration (< 3 vs. ≥ 3 years) for exploratory purposes.

To explore the impact of telemedicine on various outcomes (QoL, symptom progression, complications, caregiver burden, costs, and individual satisfaction with the personalized treatment plan), exploratory comparisons will be made between the subgroup of individuals randomized to receive personalized best medical care and individuals receiving personalized best medical care PLUS monthly and on-demand telemedicine consultations, as well as between each of these subgroups and the historical EMSA-SG cohort.

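### The sample-size SD of 0.25 belongs to an 18-month EQ-5D level, not to the change that is the primary endpoint, and the stated 80% power does not follow from it

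*Protocol article*

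**What the plan says.** All the planning inputs stand in one paragraph, Statistics, Sample size calculation. The historical EMSA-SG cohort had an "average EQ-5D score at baseline of 0.35 (95% CI 0.27–0.42"). The paragraph then reports the follow-up value of that cohort as a score "which worsened to 0.17 (95% CI 0.06–0.28) over an observational period of 18 months under standard care". Treatment is regarded as beneficial if the change in the treated group "averages 0.08 points above that of the control group at follow-up". From this the programme is expected to "limit the baseline to 18 months EQ-5D worsening to 0.25 (± 0.25 standard deviation, SD") in the patients who receive it. "With an assumed significance level of 5% and a power of 80"%, the article arrives at 46 patients, "including an expected drop-out rate of 10% over the study course".

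The primary outcome in Table 1 (Introduction) is "Baseline to 18-months EQ-5D-5L score change". Analysis sets and subgroups says the comparison is with EMSA-SG patients "matched by age (± 5 years), sex, and disease duration (± 12 months"), after the five-level responses have been grouped to match the three-level version used historically. Study design says the historical data are held at the study's own institution.

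The article gives no SD of change, correlation between visits, sidedness, matching ratio or number of EMSA-SG patients with 18-month data.

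**The concern.** Read literally, a worsening held to 0.25 would be a larger decline than the 0.18 seen under standard care, which is the opposite of the hypothesis. Read coherently, 0.25 is the level expected at 18 months, and the SD printed beside it is the SD of a level. The power of a comparison of changes depends on the SD of the change, and that differs from the SD of a level unless the two visits are correlated in a particular way.

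What is at stake is how the result will be read. If the trial is believed to have 80% power for a difference of 0.08 but has far less, a null result will be taken as evidence of no benefit when the study could not have shown one. Repairing only the power formula while keeping 0.25 would still leave an input that has not been tied to the endpoint.

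**Working it through.** **Inputs (Sample size calculation).** Historical means 0.35 (0.27 to 0.42) and 0.17 (0.06 to 0.28); difference 0.08; SD 0.25; alpha 5%; power 80%; 46 patients less 10%, so 46 × 0.9 = 41.4, about 41 completers.

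**What 0.25 is.** Historical worsening: 0.35 − 0.17 = 0.18. Expected 18-month level under the programme: 0.17 + 0.08 = 0.25. Expected worsening from the same baseline: 0.35 − 0.25 = 0.10, which is 0.08 better than 0.18.

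**Can 46 be reproduced?** Patients needed for difference 0.08, SD 0.25 and 80% power (normal approximation):

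| Comparison | Before drop-out | With 10% drop-out |
|---|---|---|
| Two groups 1:1, two-sided (per group) | 154 | 172 |
| Two groups 1:1, one-sided (per group) | 121 | 135 |
| One sample against a fixed value, two-sided | 77 | 86 |
| One sample against a fixed value, one-sided | 61 | 68 |

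None gives 46. The number does appear for a one-sided, one-sample t-test of 0.25 against the baseline value 0.35 (difference 0.10): 41 patients, and 41/0.9 = 45.6, rounded up to 46. That is not the comparison the article describes, and the article does not say it was used.

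**Power with 41 completers, 0.25 taken as the SD of change (noncentral t, two-sided 5%).**
- 41 versus 41 controls: noncentrality 0.08 / (0.25 × √(2/41)) = 1.45; power 30%.
- Historical mean treated as fixed: 0.08 × √41 / 0.25 = 2.05; power 52%.

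For 80% power at 0.08, two-sided, the SD of change would have to be about 0.13 (41 versus 41) or 0.18 (fixed mean).

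**If 0.25 is instead the level SD at both visits.** SD of change = 0.25 × √(2(1 − r)), where r is the correlation between visits (assumed, not in the article). For r = 0.3 / 0.5 / 0.7 / 0.8 it is 0.30 / 0.25 / 0.19 / 0.16, and power at 41 versus 41 is about 23% / 30% / 46% / 63%. Reaching 80% needs r of about 0.87.

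**Is 0.25 plausible against the historical intervals?** Assume each interval is mean ± 1.96 SE.
- Baseline: SE = 0.15/3.92 = 0.038; SD 0.25 corresponds to (0.25/0.038)² ≈ 43 patients (unrounded SE).
- 18 months: SE = 0.22/3.92 = 0.056; SD 0.25 corresponds to (0.25/0.056)² ≈ 20 patients (about 23 with t quantiles).
- If 41 patients lay behind both intervals, the level SDs would be 0.038 × √41 = 0.245 and 0.056 × √41 = 0.36.

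In that 41-patient case, SD of change = √(0.245² + 0.36² − 2r × 0.245 × 0.36):

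| r (assumed) | SD of change | Power, 41 vs 41, difference 0.08 |
|---|---|---|
| 0.3 | 0.37 | 16% |
| 0.5 | 0.32 | 20% |
| 0.7 | 0.26 | 29% |
| 0.72 | 0.25 | 30% |
| 0.8 | 0.22 | 37% |

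**Detectable difference at 80% power, 41 versus 41.** Approximately 2.8 × SD × √(2/41), plus a small t correction: about 0.16 at SD 0.25 and 0.20 at SD 0.32.

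**The case against.** A reader might go further and infer that the SD of 0.25 and the historical interval contradict each other: either only about 20 EMSA-SG patients had 18-month data, so controls cannot be found for 41 completers, or the SD is simply wrong. The document does not support that. The SD is stated for patients receiving the programme and the interval belongs to EMSA-SG; a single-centre cohort selected on life expectancy and comorbidity may have a different spread from a ten-country one. The interval may be model-based. No matching ratio is fixed, reuse of controls is not excluded, a coarser fallback match is provided, and linear mixed models are allowed, which can use patients without an 18-month value. The historical number is not given. Nor does a level SD of 0.36 rule out 0.25 as an SD of change: in the 41-patient case it is reached at a correlation of about 0.72. All of this stands, and it reduces the interval check to a caution.

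Two further points can be made for the plan. The article condenses a fuller protocol, where the derivation of the SD may be given. That may explain a missing source, but not a printed sentence that calls a level a worsening, or a power that the printed inputs do not produce. Also, sidedness is not stated, and a one-sided test would do better. It would, but still reaches only about 42% at 41 versus 41 and about 64% against a fixed mean.

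**Conclusion.** The sample-size paragraph is wrong as written on two counts. Its only SD is attached to an 18-month level that it describes as a worsening, with no SD for the endpoint actually compared. And 80% power does not follow from its inputs: with 0.25 accepted as the SD of change, power for 0.08 is about 30% against 41 matched controls and about 52% at best with a fixed historical mean (two-sided 5%, 41 completers).

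Most of that shortfall is already present at SD 0.25. Whether 0.25 is itself too small is open. The 18-month interval points that way if it is a plain mean ± 1.96 SE interval from appreciably more than 20 patients and the correlation between visits is below about 0.72, but neither condition can be checked from the article.

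**What to change.** In Sample size calculation:
1. Reword the sentence so that 0.25 is the expected 18-month level, with an expected worsening of 0.10 against 0.18 historically.
2. Replace the SD with that of the baseline-to-18-month change in the three-level EQ-5D index, computed from the individual EMSA-SG data, and name that source.
3. State how many EMSA-SG patients have EQ-5D at both visits, the matching ratio that number allows, and whether the test is one- or two-sided.
4. Restate the power for 0.08, or the difference detectable with 80% power, for the matched comparison with that SD and that number of controls.

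The cost is one analysis of data already held and a rewritten paragraph. Recruitment need not change. The downside is a less favourable stated power, which is best on record before the outcome data are analysed.

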### Data analysis

The distribution of quantitative data will be assessed using the Shapiro–Wilk test. Quantitative variables will be reported as mean (± SD) for normally distributed data or median (interquartile range, IQR) for non-normally distributed data, and qualitative variables as counts (percentages). Qualitative variables will be compared using Pearson’s Χ^2^ test (or Fisher’s exact test, if n < 5) and quantitative variables using the Mann–Whitney U or t-test, depending on the data distribution. A Benjamini–Hochberg correction will be applied for multiple tests, whenever appropriate. Binary logistic regression with a receiver operating characteristics (ROC) area under the curve (AUC) calculation will follow univariate analysis when applicable.

Changes in EQ-5D, motor, and non-motor scores between the MeDeMSA Care cohort and age-, sex-, and disease duration-matched historical EMSA-SG individuals will be evaluated with ANOVA for repeated measurements or linear mixed models, as most appropriate. Comparisons between randomization groups and the historical cohort will be run on a descriptive basis, with post-hoc tests adjusting for type-1 error based on ANOVA results.

QoL and caregiver burden changes in caregivers of MSA individuals receiving personalized best medical care with or without telemedicine will be analysed with ANOVA or linear mixed models, adjusted for the disease stage of the cared-for individual with MSA. Correlation analyses will assess the relationship between the caregivers’ QoL and burden with the disease characteristics (e.g., symptom constellation and severity) of the cared-for individual with MSA.

Statistical analysis will be performed with SPSS version 30.0.0 or future releases. P values below 0.05 will be considered statistically significant, with 95% confidence intervals considered where appropriate.

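### The stated inputs (difference 0.08, SD 0.25) do not give 80% power with 46 patients against the historical cohort; without a strong unstated correlation, power is about 30% to 64%

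*Protocol article*

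**What the plan says.** The sample size section of the protocol article starts from the historical EMSA-SG cohort, whose mean EQ-5D was 0.35 at baseline, "which worsened to 0.17 (95% CI 0.06–0.28) over an observational period of 18 months under standard care". It counts a treatment as beneficial "if the EQ-5D score change in the interventional group averages 0.08 points above that of the control group at follow-up", and so expects the programme to "limit the baseline to 18 months EQ-5D worsening to 0.25 (± 0.25 standard deviation, SD"). It then concludes: "With an assumed significance level of 5% and a power of 80%, 46 individuals with MSA should therefore enroll in the trial", "including an expected drop-out rate of 10% over the study course". The same sentence ties this number to showing an effect against the standard care of the historical cohort.

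Table 1 and the section on analysis sets confirm that the primary comparison is between the prospective cohort and historical patients matched on age, sex and disease duration. The outcome is the change from baseline to 18 months. The data analysis section names repeated-measures ANOVA or a linear mixed model and adds that "P values below 0.05 will be considered statistically significant". The article does not state sidedness, the number of controls per patient, the SD of the change, or any correlation.

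**The concern.** A difference of 0.08 with SD 0.25 is a standardised difference of 0.32. About 41 completers is far too few to detect that with 80% power when the comparator is another sample with its own error. The section gives a difference, an SD, a significance level and a drop-out rate and attaches a power to them, so the issue is a stated figure that does not follow from its inputs. It is not detail that an analysis plan would supply.

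The stated power is what readers will use to interpret a non-significant result. With 41 patients in each cohort and SD 0.25, the 95% CI for the difference extends about 0.11 either side. An observed benefit of exactly 0.08, the plan's own threshold, would then not be significant. The section on future directions intends to carry the findings to policymakers and guideline developers, so a null result read against a claimed 80% power could count unfairly against the care model.

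**Working it through.** **Inputs (sample size section).** Difference 0.25 - 0.17 = 0.08; as changes, (0.25 - 0.35) - (0.17 - 0.35) = -0.10 - (-0.18) = 0.08. SD 0.25. Alpha 5%. Power 80%. Enrolled 46; 46 × 0.9 = 41.4, so about 41 completers. Standardised difference d = 0.08/0.25 = 0.32.

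**Assumptions where the article is silent.** SD 0.25 applies to the analysed quantity in both cohorts; t-tests; sidedness and control ratio varied as shown.

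**Trying to reproduce 46.**
- Two cohorts 1:1, two-sided. The normal approximation is n = 2(1.960 + 0.842)²/0.32² = 153.3, so 154 per cohort. The t-test gives 154.3, so 155.
- Historical mean as a known constant, two-sided. The normal approximation is n = (1.960 + 0.842)²/0.32² = 76.6. The t-test gives 78.6, so 79, or 79/0.9 = 88 enrolled.
- The same, one-sided: 61.8, so 62, or 62/0.9 = 69 enrolled.

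None of these gives 46.

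**Power actually available.** Noncentrality is d/√(1/n₁ + 1/n₂) for two cohorts and d√n for a fixed historical mean. For 1:1 it is 0.32/√(2/41) = 1.45, against a critical value of 1.99.

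| Comparison, 41 completers | Two-sided | One-sided |
|---|---|---|
| 1 control per patient | 30% | 42% |
| 2 controls per patient | 38% | 51% |
| 3 controls per patient | 42% | 55% |
| 4 controls per patient | 45% | 57% |
| Historical mean fixed | 52% | 64% |

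If all 46 complete, the 1:1 two-sided figure is 33% and the most favourable cell is 69%.

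**Precision and detectable difference (SD 0.25, 41 completers).** 95% CI half-width at 1:1: 1.99 × 0.25 × √(2/41) = 0.110. Difference detectable with 80% power, two-sided: 0.157 at 1:1 and 0.112 with a fixed historical mean.

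**What would rescue 80% (two-sided).** Three routes were solved:
- Matched pairs, SD of the pair difference 0.25√(2(1 - r)), 41 pairs: within-pair r of about 0.75.
- Baseline-adjusted comparison, residual SD 0.25√(1 - r²), 41 per cohort: baseline to 18-month r of about 0.86.
- Three controls per patient, change scores with SD 0.25√(2(1 - r)): r of about 0.8.

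**If 0.25 is the SD of a single score and raw changes are compared.** At 41 versus 41, power is 17% at r = 0, 30% at r = 0.5, 46% at r = 0.7 and 62% at r = 0.8.

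**The case against.** The strongest reply is that 30% is not the plan's own number. It needs a two-sided test, one control per patient, and 0.25 as the SD of the analysed quantity in both cohorts, and the article states none of these. The printed 0.25 is attached to the 18-month score, while the outcome is a change, so power depends on a correlation that is not given. A fuller protocol may supply these items. This stands against any single figure, and the result is therefore given as a range. It does not save the 80%: relaxing sidedness, control ratio and control uncertainty together still gives at most 64%. What remains is a strong correlation, of which the article says nothing. Matching on age, sex and disease duration alone is unlikely to give a within-pair correlation of 0.75.

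Some stronger readings are tempting but not supported:
- **That 46 came from testing the wrong hypothesis.** A one-sided one-sample test of the fall from 0.35 to 0.25 (0.10/0.25 = 0.40) gives n = 41, and 41/0.9 = 46. But a one-sided test of change against a fixed -0.18 with r = 0.68 has SD 0.25√(2 × 0.32) = 0.20, so d is again 0.40 and n again 46, and it targets the 0.08 benefit. The origin cannot be determined.
- **That the SD contradicts the quoted confidence intervals.** The intervals belong to the historical cohort and the SD to the new one. With SD 0.25, the half-width of 0.11 at 18 months would imply (1.96 × 0.25/0.11)² = 19.8, about 20 historical patients. A larger number would mean a larger SD. The article does not give the number, so this is a point to check and not an error.
- **That the phrase "the MeDeMSA Care program to limit the baseline to 18 months EQ-5D worsening to 0.25" describes a fall larger than the historical 0.18.** The preceding sentence uses the same construction for a score, and the 0.08 gap confirms that 0.25 is a score. This is wording only.
- **That the sponsor will read a null result as no effect.** Nothing in the article says so; it is a foreseeable consequence of the stated power.

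**Conclusion.** The concern holds in this form: 80% power with 46 enrolled does not follow from a 0.08 difference with SD 0.25 in the comparison with the historical cohort. With about 41 completers, two-sided power is about 30% at 1:1, 38% to 45% with two to four controls per patient, and 52% with the historical mean treated as known (64% one-sided). These figures assume that 0.25 is the SD of the analysed quantity in both cohorts and that correlation brings no gain. Power would be lower than the 1:1 figure for raw change scores if 0.25 is a single-score SD and the baseline to 18-month correlation is below 0.5. It would reach 80% only with correlations of the order of 0.75 to 0.86, depending on the analysis and number of controls. The true figure can be settled from individual data that the centre already stores.

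**What to change.** Keep 46 patients and rewrite the sample size paragraph:

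1. State the target as a difference in change, -0.10 versus -0.18.
2. Take the SD of the 18-month change and the baseline to 18-month correlation from the stored EMSA-SG individual data. At the same time, record how many historical patients have an 18-month value, which settles the SD and confidence interval question.
3. State the test, its sidedness and the control ratio. Use all eligible historical controls with adjustment for baseline EQ-5D.
4. Replace 80% with the achievable power for 0.08 and the difference detectable with 80% power. If SD 0.25 is confirmed for the analysed quantity, that difference is about 0.16 at 1:1 and 0.11 with a fixed historical mean.
5. Report the primary result with its 95% CI, so that a non-significant result is read against its precision. Making the comparison estimation-only is a matter of preference and is not needed.

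The cost is one paragraph of text and a short re-analysis of data already held. No extra patients are needed, and with 23 enrolled by March 2025 the restatement could be made before the primary data are complete. The price is a less favourable stated power, unless the stored data show a strong correlation.

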## Methods

### Study design

This 18-month, monocentric, open-label study evaluates the impact of multidisciplinary, personalized best medical care, including mobile palliative and telemedicine support on the EQ-5D-5L score change of prospectively recruited MSA individuals compared to a sex-, age- and disease-duration matched historical European MSA cohort that received standard care [EMSA-SG cohort, (Wenning et al. 2013)], and whose data is stored at the Medical University of Innsbruck. The EMSA-SG cohort included individuals with MSA from ten countries, who underwent in-person assessments every six months over a 24-month period, showed largely comparable clinical-demographic characteristics across countries, but did not regularly receive treatment for MSA non-motor symptoms, neurorehabilitation, psychological counselling or palliative care offer (Kollensperger et al. 2010).

The study also assesses the participants'motor progression over 18 months using the Unified MSA Rating Scale (UMSARS) Part II through blinded video evaluations. Their progression is then compared to the motor progression curves of matched individuals from the EMSA-SG cohort.

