## Potential study limitations

MeDeMSA Care's monocentric design and MSA’s rapid progression pose recruitment and retention challenges, with risks of dropout due to treatment noncompliance or fatal events. Recruitment empowering strategies are therefore regularly implemented. The re-assessment of the patient’s health-care goals at month-12 should also minimize the risk of incompliance. In case the drop-out rate will exceed current estimations, recruitment may be extended to achieve the targeted population size. To ensure continuity of care, individuals not randomized to the telemedicine arm may replace in-person follow-ups with telemedicine visits if disease progression prevents travel. While this safeguards ongoing care to the individuals participating in the MeDeMSA Care study, it may introduce a retention bias, favoring more severe cases that would have likely been lost to follow-up in the EMSA-SG study.

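### The 10% drop-out has no stated basis and looks optimistic beside the widening historical intervals, and 46 patients do not give 80% power for 0.08 even if it holds

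*Protocol article*

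**What the plan says.** The sample size rests on the historical EMSA-SG cohort, which had an "average EQ-5D score at baseline of 0.35 (95% CI 0.27–0.42"), "which worsened to 0.17 (95% CI 0.06–0.28) over an observational period of 18 months". A useful effect is one where the intervention group "averages 0.08 points above that of the control group at follow-up". The programme is expected to "limit the baseline to 18 months EQ-5D worsening to 0.25 (± 0.25 standard deviation, SD"). Since 0.17 + 0.08 = 0.25, the first 0.25 is read here as the expected 18-month level.

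With 5% significance (sidedness not stated) and 80% power, the result is 46 patients, "including an expected drop-out rate of 10% over the study course". The primary outcome in Table 1 is the change from baseline to 18 months against matched historical patients.

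Under Potential study limitations, the article names retention as a challenge, "with risks of dropout due to treatment noncompliance or fatal events", and says that recruitment may be extended if drop-out exceeds the estimate. Under Study design, it describes the historical cohort as one "whose data is stored at the Medical University of Innsbruck".

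**The concern.** The plan takes its means and its effect from the historical cohort, but not its attrition. The 10% stands without a source, in a fatal disease, in a study that also enrols wheelchair-bound patients, with an endpoint 18 months away. The cohort's own interval is about 1.47 times as wide at 18 months as at baseline. The width of an interval for a mean depends on the SD and the number observed, so the numbers fell, the SD rose, or both. Either would be unwelcome for a plan built on small loss and one SD.

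Patients without an 18-month value add little to the primary contrast. If many historical patients lack that value, the pool of usable matched controls also shrinks, whatever retention this trial achieves. A null result from an underpowered comparison could then be misread as evidence that the programme does not help.

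**Working it through.** **Inputs** (all from Sample size calculation): difference 0.08; SD 0.25; 5% significance; 80% power; 10% loss; 46 enrolled; historical intervals 0.27–0.42 and 0.06–0.28. The number of controls and the matching ratio are not given.

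**1. The plan's own figure.** The drop-out step is sound: 41/0.9 = 45.6, rounded up to 46. The 41 does not follow from 0.08 and SD 0.25. Using the normal formula with two-sided 5% and 80% power:

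- Fixed historical mean: n = [(1.960 + 0.842) × 0.25/0.08]² = 76.7, so 77, and 77/0.9 gives 86 enrolled.
- Independent 1:1 controls: n = 2 × 76.7 = 153.3, so 154, and 154/0.9 gives 172 enrolled.
- One-sided, these become 68 and 135.

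The only variant found that gives 46 without a further assumed input is a one-sided one-sample t-test of 0.35 against 0.25 (difference 0.10, SD 0.25), which needs 41. That is a within-group change, not the comparison described. Matched pairs would need a within-pair correlation of about 0.7, which is not stated.

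**2. What the historical intervals imply.** With SE = width/3.92:

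- Baseline: 0.15/3.92 = 0.0383. At 18 months: 0.22/3.92 = 0.0561.
- Since SE = SD/√n, n₁₈/n₀ = (SD₁₈/SD₀)² × (0.15/0.22)² = (SD₁₈/SD₀)² × 0.465.

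| SD₁₈/SD₀ | Implied retention | Implied loss |
|---|---|---|
| 1.0 | 46% | 54% |
| 1.1 | 56% | 44% |
| 1.2 | 67% | 33% |
| 1.3 | 79% | 21% |
| 1.39 | 90% | 10% |

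The last row comes from √0.9 × 0.22/0.15 = 1.39. Rounding of the printed limits alone (widths 0.14–0.16 and 0.21–0.23) moves the constant-SD loss between 42% and 63%.

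**3. Power for 0.08 with SD 0.25, two-sided 5%.** This uses the non-central t distribution, with non-centrality (0.08/0.25)√n against a fixed mean and (0.08/0.25)√(n/2) against 1:1 controls.

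| Loss from 46 | Evaluable | Fixed historical mean | 1:1 controls |
|---|---|---|---|
| 0% | 46 | 57% | 33% |
| 10% | 41 | 52% | 30% |
| 30% | 32 | 42% | 24% |
| 54% | 21 | 29% | 17% |

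One-sided at n = 41, the figures are 64% and 42%.

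**4. Detectable difference at n = 41** (two-sided, 80% power, normal formula): 2.802 × 0.25/√41 = 0.109 against a fixed mean; 0.109 × √2 = 0.155 against 1:1 controls. To detect 0.08, the SD would have to be 0.183 or 0.129 respectively.

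**The case against.** A reader might infer that the 10% and the quoted intervals contradict each other. They do not. The article gives neither the historical SDs nor the numbers seen at each visit, and it does not say whether the intervals are raw or model-based. A 1.39-fold rise in SD reconciles them with 10% loss. Nor does the plan assume a constant SD in the historical cohort, since the 0.25 is attached only to the expected result in the MeDeMSA Care group. The 42–63% range reflects rounding at an SD ratio of exactly 1, so it is not a full uncertainty range.

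A reader might also take the historical loss as a forecast for this trial. That is not supported either. The historical patients had standard care and in-person assessments. This trial requires an expected survival of at least 24 months, excludes a Charlson index above 4, lets patients who cannot travel complete assessments online, and foresees extended recruitment. The article itself expects to keep severe cases that the historical study would probably have lost. The mixed models allowed under Data analysis would also use month 6 and 12 values from patients who leave early.

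These objections stand, and they rule out any claim that the trial will end with about half its patients. They do not supply a basis for 10%: none of these features is offered as its source, and extending recruitment is optional and would leave the SD unchecked. They also do not affect the power shortfall, which is present with no drop-out at all.

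**Conclusion.** Two statements hold. First, the 10% is unsupported and looks optimistic. The quoted intervals imply a historical loss anywhere from about 54% (constant SD) through 33% (SD up by 20%) to 10% (SD up 1.39-fold), and the article does not let the reader choose among these. Second, the stated 80% power is not delivered even at the planned loss: about 52% against a fixed historical mean, which is the favourable case because it ignores the sampling error of that mean, and about 30% against 1:1 controls.

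It would be tempting to blame drop-out for the power shortfall. That would be wrong: with all 46 evaluable, two-sided power is still only about 57% at best. Higher loss makes an existing gap larger.

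The power figures assume two-sided 5%, SD 0.25 for the quantity compared, independent groups in the 1:1 case, and complete 18-month data among the evaluable. Strong within-pair correlation or a smaller SD of change would raise them, but the article states neither.

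**What to change.** From the historical records held at the centre, restricted to patients who would meet this trial's entry criteria, count how many have an EQ-5D value at 18 months and compute the SD of the 18-month change in the same patients. Use these in place of the unsourced 10% and the SD of 0.25. If they cannot be obtained, state a range of loss such as 10%, 30% and 50%. Where the expected loss is set below the historical figure, say which design features justify that.

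Then restate the evaluable number, the power for 0.08 and the detectable difference for 46 enrolled, naming the contrast (fixed mean, or matched controls with their ratio) and the sidedness of the test.

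The work is one query on data already held and a revised paragraph. It needs no extra patients and no change in conduct. The downside is that the stated power will probably be less favourable.
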